## Abstract

**Background:**

Rheumatoid arthritis (RA) and psoriatic arthritis (PsA) are inflammatory diseases that often affect the wrist and, when affected, can lead to impaired wrist function and progressive joint destruction if inadequately treated. Standard care consists primarily of disease-modifying anti-rheumatic drugs (DMARDs), often supported by systemic corticosteroids or intra-articular corticosteroid injections (IACSI). IACSI, despite their use worldwide, show poor response in a substantial group of patients. Arthroscopic synovectomy of the wrist is the surgical removal of synovitis with the goal to relieve pain and improve wrist function. The primary objective of this study is to evaluate wrist function following arthroscopic synovectomy compared to IACSI in therapy-resistant patients with rheumatoid or psoriatic arthritis. Secondary objectives include radiologic progress, disease activity, health-related quality of life, work participation and cost-effectiveness during a 1-year follow-up.

**Methods:**

This protocol describes a prospective, randomized controlled trial. RA and PsA patients are eligible with prominent wrist synovitis objectified by a rheumatologist, not responding to at least 3 months of conventional DMARDs and naïve to biological DMARDs. For 90% power, an expected loss to follow-up of 5%, an expected difference in mean Patient-Rated Wrist Evaluation score (PRWE, range 0–100) of 11 and *α* = 0.05, a total sample size of 80 patients will be sufficient to detect an effect size. Patients are randomized in a 1:1 ratio for arthroscopic synovectomy with deposition of corticosteroids or for IACSI. Removed synovial tissue will be stored for an ancillary study on disease profiling. The primary outcome is wrist function, measured with the PRWE score after 3 months. Secondary outcomes include wrist mobility and grip strength, pain scores, DAS28, EQ-5D-5L, disease progression on ultrasound and radiographs, complications and secondary treatment. Additionally, a cost-effectiveness analysis will be performed, based on healthcare costs (iMCQ questionnaire) and productivity loss (iPCQ questionnaire). Follow-up will be scheduled at 3, 6 and 12 months. Patient burden is minimized by combining study visits with regular follow-ups.

**Discussion:**

Persistent wrist arthritis continues to be a problem for patients with rheumatic joint disease leading to disability. This is the first randomized controlled trial to evaluate the effect, safety and feasibility of arthroscopic synovectomy of the wrist in these patients compared to IACSI.

**Trial registration:**

Dutch trial registry (CCMO), NL74744.100.20. Registered on 30 November 2020.

ClinicalTrials.gov NCT04755127. Registered after the start of inclusion on 15 February 2021.

**Supplementary Information:**

The online version contains supplementary material available at 10.1186/s13063-023-07129-y.

## Administrative information

Note: the numbers in curly brackets in this protocol refer to SPIRIT checklist item numbers. The order of the items has been modified to group similar items (see http://www.equator-network.org/reporting-guidelines/spirit-2013-statement-defining-standard-protocol-items-for-clinical-trials/).

## Introduction

### Background and rationale {6a}

Rheumatoid arthritis (RA) and psoriatic arthritis (PsA) are common forms of chronic immune-mediated inflammatory arthritis with estimated prevalences of 1 and 0.1% respectively in Western countries [1, 2]. Wrist involvement is a common feature of RA and has been reported to occur in 50% of patients in the first 2 years after disease onset [3]. Like RA, PsA is a chronic joint disease that is characterized by synovial hyperproliferation of several joints. Differentiation between RA and PsA can be challenging due to similarities in their clinical presentation [4, 5]. When inadequately treated, both RA and PsA can lead to progressive joint destruction, functional disabilities and reduced quality of life [6].

First-line treatment of RA and PsA consists of conventional (c) disease-modifying anti-rheumatic drugs (DMARDs), usually in combination with corticosteroids (either local or systemic). Failure to control disease activity by means of two or more cDMARDs necessitates switching to newer therapies such as biological (b) DMARDs and targeted synthetic (ts) DMARDs, which are costly monoclonal antibodies that target specific parts of the immune system. Systemic and local corticosteroids are widely used as bridging therapy for DMARDs. Intra-articular corticosteroid injections (IACSI) have the advantage over systemic treatment in that they act in specific joints while lacking systemic toxicity [7, 8]. However, the use of IACSI has become a topic of debate due to disappointing long-term results. Recent studies have shown that IACSI achieve reduced swelling and tenderness in 40–50% of injected RA and PsA joints after 3 months and that relapse occurs in up to 40% of joints within 12 months [9–12]. Moreover, long-term differences in radiographic joint damage and disability were not found between injected and non-injected patients [9].

When individual arthritic joints remain refractory to drug therapy, surgical approaches may be indicated to preserve joint function, prevent further destruction of tendons and relieve pain [13, 14]. Tendon reconstruction, wrist arthroplasty or arthrodesis are only indicated for advanced stages of wrist arthritis due to their disabling consequences and high risk of complications [3, 15]. Synovectomy of the wrist aims to relieve symptoms and prevent disease progression by debulking inflamed synovial tissue. Arthroscopic synovectomy has shown clear advantages over open synovectomy as it renders minimal postoperative pain, early rehabilitation, faster recovery and less restriction of joint motion [13, 16]. Therefore, open synovectomy has largely been abandoned. A recent systematic review included six studies with a total of 153 wrists of RA patients that underwent arthroscopic synovectomy [17]. Improvements of wrist pain and functionality were observed after a mean follow-up of 4 years with only two complications. However, since RCTs were not available, findings were based on non-comparative cohort studies and the risk of bias was high. The efficacy, adverse effects and feasibility of arthroscopic synovectomy in rheumatic wrists remain to be investigated.

Poor response rates to DMARD therapy in RA and PsA patients have necessitated the identification of pathobiological biomarkers and immunological features that predict the outcome of treatment with biological (and targeted synthetic) DMARDs. Implementing these profiles for therapy may ultimately lead to personalized medicine and improved patient care [18, 19]. The synovium is the primary site of inflammation of RA; therefore, synovial biopsies are superior to blood or skin samples for these analyses [19]. Preferably, tissue from biological-naïve patients is used for this.

## Objectives {7}

The primary objective of this study is to evaluate the effects of arthroscopic synovectomy of the wrist in therapy-refractory patients with RA or PsA compared to IACSI. The primary objective is to compare the improvement of wrist function 3 months after the intervention, measured using the Patient-Rated Wrist Evaluation (PRWE) questionnaire. The secondary objectives are to evaluate differences over a 12-month period in range of wrist motion, grip strength, DAS28 score, reduction of synovitis on wrist ultrasound, progression of joint destruction on wrist radiographs, blood inflammation parameters and overall quality of life. Additionally, complications, secondary drug treatment and secondary surgery will be evaluated. Finally, a cost-effectiveness analysis will be performed based on healthcare-related costs (using the iMCQ questionnaire) and loss of productivity (using the iPCQ questionnaire) over a 12-month period.

### Storage of synovial tissue collected by means of wrist arthroscopy

Patients undergoing arthroscopic synovectomy will be asked to participate in a separate study, in which removed synovial tissue will be analysed by means of histology, proteomics and RNA sequencing. The objective is to identify histological and immunological disease characteristics and attempt to predict therapy response for future treatment with bDMARDs.

## Trial design {8}

The ARCTIC trial is a non-blinded, two-arm randomized controlled trial comparing arthroscopic synovectomy to IACSI of the wrist. The patient allocation ratio is 1:1. Patients of both groups are allowed to cross over after 3 months if clinically indicated.

## Methods: participants, interventions and outcomes

### Study setting {9}

The ARCTIC trial will be performed in a hospital, providing secondary and tertiary care, that is specialized in wrist arthroscopy and has a large population of rheumatic patients (Maasstad Hospital, Rotterdam). Both interventions, wrist arthroscopy and IACSI, are part of standard care. Patients will be screened in the Maasstad Hospital or pre-screened in the participating hospitals (EMC, FGV, LUMC, ASH) and referred to the Maasstad Hospital if they are eligible and willing to participate. Patients are considered for inclusion if they meet the criteria as defined below.

### Eligibility criteria {10}

#### Inclusion criteria

Patients must meet the following criteria to be eligible for the study:The patient is 18 years or older.The patient is able and willing to give written informed consent and is available for the entire study.Patients are diagnosed with RA, according to the revised 2010 ACR/EULAR Rheumatoid Arthritis Classification Criteria [20], *or* PsA, according to the CASPAR criteria [21]The patient is experiencing an exacerbation as reflected by an increase in DAS28 > 1.2 or > 0.6 if DAS28 ≥ 3.2 compared to the last DAS28 measurement (maximum 6 months before), and/or clinical assessment by a rheumatologist.The exacerbation is refractory to systemic cDMARDs for at least 3 months.Wrist arthritis is the predominant symptom.

#### Exclusion criteria

Patients that meet any of the following criteria will be excluded from participation in this study:Previous or current treatment with bDMARDsCurrent inflammatory joint disease other than RA or PsA (e.g. gout, reactive arthritis, Lyme disease)Pregnancy or intended pregnancy during the studyIntra-articular corticosteroid injection in the affected wrist in the last 3 monthsPrevious wrist surgery of the affected wristSevere osteoarthritis with malformations of the affected wristCongenital abnormalities of wrist function or motionInsufficient knowledge of the Dutch language to ensure that questionnaires can be adequately understood and completed

Note: If both wrists are affected and both are eligible, only one wrist can be included in the study. The rheumatologist and patient will together decide which wrist will be included. The other wrist will be treated according to standard care, which can include IACSI or wrist arthroscopy, depending on the choice of the rheumatologist and patient. Because the primary outcome of the study is wrist-specific, and no comparison is made between both wrists, this does not affect the study outcome (see the ‘Outcomes {12}’ section).

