#### Secondary outcomes

The following secondary outcome measures will be measured at baseline, 3 months, 6 months and 12 months (Table 1):Range of motion (ROM) of the wrist measured using a standard goniometer, including pronation, supination, ulnar and radial deviation, and palmar and dorsal flexionGrip strength of the wrist measured using a dynamometer (Saehan). Grip strength will be calculated as the mean of three attemptsNumeric Rating Scale (NRS) pain scale. A score of 0 indicates no pain, and a score of 10 indicates the worst possible painEULAR response rate and Disease Activity Score (DAS28)Resolution of synovitis measured by wrist ultrasound in grey scale and power Doppler mode (baseline and 3 months only)Wrist arthritis and joint destruction on standard (plain) radiographs of the wrist (baseline and 12 months only)Quality of life measured with the EuroQol 5D (EQ-5D-5L) questionnaireBlood parameters including erythrocyte sedimentation rate (ESR) and C-reactive protein (CRP) (part of the routine clinical care)Complications and subsequent treatment

**Table 1 Tab1:** Trial schedule according to the recommendation for interventional trial (SPIRIT) guidelines

	Enrolment	Allocation	Post-allocation					
Timepoint**	*14 days (*± *4 days) prior to intervention*	Intervention	*Week 2*	*Week 4*	*Week 6*	*Month 3*	*Month 6*	*Month 12*
Enrolment								
Eligibility screen	X							
Informed consent	X							
Allocation	X							
Interventions								
Arthroscopic synovectomy		X						
Intra-articular corticosteroid injection		X						
Assessments								
Questionnaires (PRWE, EQ-5D-5L, iMCQ, iPCQ)	X					X	X	X
Physical exam (including ROM, GS and DAS28)	X					X	X	X
Wrist ultrasound	X					X		
Plain wrist radiographs	X							X
Blood parameters (ESR, CRP)	X					X	X	X
NRS pain scores	X		X	X	X	X	X	X
Complications and secondary treatment			X	X	X	X	X	X
Cost-effectiveness analysis								X

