### Concealment mechanism {16b}

Because the study intervention involves a surgical procedure, allocation is not concealed and will be revealed to both the patient and the researcher upon randomization.

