## Assignment of interventions: Blinding

### Who will be blinded {17a}

Patients, researchers, rheumatologists and surgeons will not be blinded because the study involves a surgical procedure which requires the patient to come to the operation theatre and which will leave signs of arthroscopic surgery that will be recognizable to the outcome assessors.

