Secondary outcomes include the EULAR response rate, reduction of synovitis on wrist ultrasound, progression of wrist arthritis on plain radiography and quality of life. DAS28 scores are used to determine the EULAR response rate, which measures responsiveness to anti-rheumatic treatment. The DAS28 is a composite measure of disease activity in rheumatic patients calculated by evaluating 28 joints for swelling and tenderness, combined with NRS pain scores and C-reactive protein levels in the blood. Wrist ultrasound, performed by one of two experienced rheumatologists, is used to measure the resolution of synovitis and is scored using the EULAR-OMERACT combined scoring system which combines grey scale and power Doppler mode [33]. Ultrasound has demonstrated greater sensitivity than clinical assessment and conventional radiography for detecting synovitis in RA target joints [34, 35]. Standard wrist radiographs will be graded using the modified Larsen grading system, which scores degenerative wrist arthritis and joint destruction on a score of 0 to 5, 5 indicating the most joint abnormalities [36, 37]. The EuroQol 5D (EQ-5D-5L) questionnaire is a widely used standardized questionnaire scoring overall quality of life using five different 5-level domains, on a scale from 0 to 100. It has been validated and translated to Dutch [38, 39]. A cost-effectiveness analysis will be performed based on medical costs and productivity loss (see the ‘Methods for additional analyses (e.g. subgroup analyses) {20b}’ section). The iMTA Productivity Cost Questionnaire is a standardized instrument for measuring and valuing health-related productivity losses and estimated societal costs based on educational level, job type and lost workdays [40]. The iMTA Medical Consumption Questionnaire (iMCQ) is a standardized instrument including questions related to frequently occurring contacts with health care providers, medication use and home care [40]. Medical resource prizes will be obtained from the Dutch Healthcare Authority [41]. From these costs, cost-effectiveness will be calculated in relation to quality-adjusted life years (QALYs) using the EQ-5D-5L (or PRWE) over a 1-year and 5-year span.

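### The statement that treating the other wrist has no effect is supported for study-wrist outcomes only, not for DAS28/EULAR response, ESR/CRP, EQ-5D-5L/QALYs or per-patient costs

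*Protocol article*

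**What the plan says.** The note under Exclusion criteria in the Protocol article allows one wrist per patient. For the remaining wrist it states: "The other wrist will be treated according to standard care, which can include IACSI or wrist arthroscopy", at the discretion of rheumatologist and patient. It then concludes: "Because the primary outcome of the study is wrist-specific, and no comparison is made between both wrists, this does not affect the study outcome", and refers the reader to Outcomes {12}.

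That section gives the PRWE as the primary outcome and then lists secondary outcomes, some tied to a wrist and some to the whole patient. Objectives {7} confirms that they matter: "The secondary objectives are to evaluate differences over a 12-month period in range of wrist motion, grip strength, DAS28 score", followed by blood inflammation parameters, quality of life and cost-effectiveness among others. The DAS28 is "calculated by evaluating 28 joints for swelling and tenderness, combined with NRS pain scores and C-reactive protein levels in the blood". Under Cost-effectiveness analysis, direct and indirect costs are collected per patient and include surgical admissions.

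On allocation, Concealment mechanism {16b} says that "allocation is not concealed and will be revealed to both the patient and the researcher upon randomization", and Who will be blinded {17a} says: "Patients, researchers, rheumatologists and surgeons will not be blinded".

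**The concern.** The premise concerns the primary outcome, while the conclusion is worded for the study outcome and points to a section that also lists patient-level outcomes. A wrist-specific PRWE gives no assurance about a 28-joint score, a blood marker, a quality-of-life index or a patient's total bill.

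It also matters when the other wrist's treatment is chosen. If that happens after the arm is known, the choice may depend on the arm. A bilateral patient allocated to injection might, for example, have the other wrist operated on. Part of the difference between arms in the patient-level outcomes and in the ICER would then come from the other wrist. The protocol takes care over co-intervention elsewhere, but in its only text on the other wrist it sets the issue aside.

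**Working it through.** **1. The plan's own figure.** Sample size {14} uses a difference of 11.0 PRWE points, SD 15.0, correlation 0.1, two-sided alpha 0.05 and power 90%. With baseline in the outcome vector and a common baseline mean, the effective SD is 15 × √(1 − 0.1²) = 14.92. Then n = 2 × (1.960 + 1.282)² × 14.92² / 11² ≈ 38.7, or 39 per arm, against the stated 38 from simulation. Allowing 5% loss, 38 / 0.95 = 40. The figure reproduces closely. It rests on the PRWE alone, so this point does not change it.

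**2. Which outcomes the stated reason covers.**

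| Outcome | Measured on | Covered? |
|---|---|---|
| PRWE, range of motion, grip strength, wrist ultrasound, wrist radiographs | study wrist | yes |
| DAS28 and EULAR response | 28 joints, pain and CRP | no |
| ESR, CRP | blood | no |
| EQ-5D-5L, and QALYs built on it | whole patient | no |
| Direct and indirect costs | whole patient | no |

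**3. Whether the choice can depend on the arm.** Table 1 places allocation at the enrolment visit, 14 ± 4 days before the intervention, so the arm is known 10 to 18 days ahead. The note sets no time for the other-wrist decision. Criteria for discontinuing or modifying {11b} defers further treatment of the wrist until after 3 months. Concomitant care {11d} fixes DMARDs and systemic corticosteroids for 3 months. Neither mentions local treatment of the other wrist. Table 1 has a row "Complications and secondary treatment", but it is not tied to one wrist or the other.

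**4. What governs the size.** The shift in a patient-level arm difference is (share with bilateral disease) × (between-arm difference in other-wrist treatment) × (effect or cost of that treatment per patient). The document gives none of the three. On assumed values:

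- 20% bilateral and a 10-point difference between arms: 0.20 × 0.10 = 2% of the per-patient effect or cost.
- 60% bilateral and a 50-point difference: 0.60 × 0.50 = 30%.
- No difference between arms: zero.

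In counts, let k be other-wrist arthroscopies in the IACSI arm minus those in the synovectomy arm, with 40 per arm. The mean cost difference moves by −k/40 of one arthroscopy cost: 0.025 at |k| = 1 and 0.10 at |k| = 4.

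**5. Why this does not become an ICER estimate.** Let D be the incremental cost in units of one arthroscopy, and rE the QALY gain from an other-wrist operation relative to the between-arm QALY difference. The ICER is multiplied by [1 − (k/40)/D] / [1 − (k/40) × rE]. All three inputs are assumed.

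| k | D | rE = 0 | rE = 1 |
|---|---|---|---|
| +4 | 0.5 | −20.0% | −11.1% |
| +4 | 2 | −5.0% | +5.6% |
| −4 | 0.5 | +20.0% | +9.1% |
| −4 | 2 | +5.0% | −4.5% |

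Even the sign depends on the assumptions, so these figures only illustrate the mechanism.

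**The case against.** The strongest reply is that the sentence is right as meant. Its premise is the primary outcome, its conclusion is singular, and the section it points to opens with the primary outcome. On that reading nothing in it is false. This stands: the wording is ambiguous and not plainly wrong, which keeps the point minor.

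The imbalance is also hypothetical. It needs bilateral eligible disease, a decision taken after allocation, and a net difference between arms. Explanation for the choice of comparators {6b} calls injection the first choice for refractory joints and says that synovectomy is not regularly used for this indication. Injection is therefore the likelier treatment of the other wrist in both arms. This stands too, and is the main reason to expect a small effect. Arthroscopy of the other wrist is nevertheless expressly allowed.

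Counting all patient costs is legitimate. Under intention to treat, other-wrist care that follows from the allocated strategy can be seen as part of its effect. That is defensible, but the contrast is then no longer attributable to the study wrist alone, and a reader needs other-wrist treatment by arm to see this. Some of the data capture may be in the full protocol, which is not shown. Its absence from the article is not the fault claimed here.

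A reader might go further and infer an inflated false-positive rate for DAS28. Taking the 0.6 and 1.2 eligibility thresholds as the effect of treating one wrist, with |k| = 4 and an assumed SD of 1.0 to 1.3, would turn 5% into 5.5% to 8.4%. The document does not support this. Those thresholds define a flare in the whole patient, while the wrist is one of 28 joints scored.

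**Conclusion.** The point holds in limited form. The stated reason justifies the no-effect statement for the PRWE and other study-wrist measures. It does not justify it for DAS28/EULAR response, ESR/CRP, EQ-5D-5L/QALYs or per-patient costs. Because allocation is open and the timing of the other-wrist decision is not fixed, an arm-dependent choice is possible and could bias these secondary and economic comparisons.

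The size cannot be derived from the document. It is probably small, and it is zero if the uptake and type of other-wrist treatment are balanced. A reader might infer that the primary result is compromised or that treating the other wrist should be prohibited. Neither follows: the PRWE analysis and the sample size are untouched, and standard care of the other wrist can stay. This is a minor improvement.

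**What to change.** - Reword the note so that the no-effect statement applies to wrist-specific outcomes only.
- For bilateral patients still to be enrolled, decide and record the other wrist's planned treatment before randomisation. It then becomes a baseline feature that cannot depend on the arm.
- Report other-wrist treatment actually given, by arm.
- Count complications and secondary interventions for the study wrist separately from those of the other wrist.
- Optionally, add an ICER without other-wrist procedure costs as a sensitivity analysis.

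The cost is a wording change, one baseline eCRF item and a record of other-wrist treatment, with no added visits or patients. The downside is that some patients will later depart from the recorded plan for clinical reasons. Those departures should be allowed and reported. Recruitment began in January 2021, so the pre-randomisation step cannot reach patients already enrolled. For them, other-wrist procedures done at the trial hospital could be sought in its records. Adjusting for bilateral disease at baseline may add precision but would not remove bias from arm-dependent treatment.
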